## 7. STUDY DESIGN

NEON is a multicentre randomised controlled trial with 1:1 allocation. Participants and follow-up assessors will be blinded to the randomised allocation.

Participants will be recruited to the study in hospitals across the UK. The study overall is modelled on 25 centres, but additional sites may be included depending on recruitment rates in the 9 month recruitment pilot phase.

Participants are expected to be enrolled in the study for up to 24 months. During the first 12 months the participants will attend follow-up clinic visits and complete questionnaires as per the schedule in Appendix

A and flow diagram (Figure 1). Routine data will be collected during the second 12 months via HES data and the Reconstructive Surgical Trainees Network (RSTN).

[figure not shown]

**Figure 1:** Participant flow diagram for NEON study

## 7.1. Pilot Phase

Incorporated within the NEON study design is a recruitment pilot phase, which will involve up to 9 centres with a staggered initiation over a period of 9 months. The aim of the pilot is to assess the following criteria: recruitment rate; ability to maintain assessor and participant blinding; adherence to the randomised procedure and early retention rates. The initial 9 centres will be used as a basis for revising aspects of study conduct.

Screening forms containing eligibility, reasons for exclusion and patients declining to participate will be completed. Rates of consent withdrawal and compliance with the randomised allocation will also be recorded. Any obvious barriers to recruitment will be assessed at 9 months. The overall recruitment target for the pilot is 44 participants, based on one participant per site per month with staggered site initiation.

The study team and oversight committees will consider all aspects of study conduct and any new evidence as the study moves into the definitive phase. Based on how the above criteria are met, the study team and committees will consider whether substantial changes are needed, and ultimately consider the viability of the study as currently designed and funded. Specific examples of this are seen in Table 1. Major changes derived from pilot work will be discussed with the appropriate stakeholders.

**Table 1:** Success criteria within the pilot study

|                                                                                                           | Red                                                                                                   | Amber                                                                                                                                             | Green                                                                        |
|-----------------------------------------------------------------------------------------------------------|-------------------------------------------------------------------------------------------------------|---------------------------------------------------------------------------------------------------------------------------------------------------|------------------------------------------------------------------------------|
| Recruitment                                                                                        |                                                                                                       |                                                                                                                                                   |                                                                              |
| Sites open
target = 9                                                                    | 2 (22%)                                                                                               | 4 (44%)                                                                                                                                           | 7 (78%)                                                                      |
| Recruitment rate
target = 44, based on 1 per site per month, with staggered site opening | 10 (23%)                                                                                              | 22 (50%)                                                                                                                                          | 33 (75%)                                                                     |
| Action                                                                                             | Use other pilot data and patient focus group to inform discussion with TSC to consider stopping trial | Use other pilot data and patient focus group to inform discussion with TSC regarding strategies for improvement and consider changes to processes | Proceed to main trial – consider focus group feedback and other pilot data.  |
| Adherence                                                                                          |                                                                                                       |                                                                                                                                                   |                                                                              |
| Adherence to randomised procedure                                                                  | 10 (23%)                                                                                              | 22 (50%)                                                                                                                                          | 38 (85%)                                                                     |
| Action                                                                                             | Consider screening log data and feedback from sites and discuss with TSC to consider stopping trial   | Consider screening log data and feedback from sites and discuss with TSC strategies for improvement and consider changes to processes             | Proceed to main trial – consider screening log data and feedback from sites. |

| Retention                                                          |                                                                                                       |                                                                                                                                                   |                       |
|--------------------------------------------------------------------|-------------------------------------------------------------------------------------------------------|---------------------------------------------------------------------------------------------------------------------------------------------------|-----------------------|
| PROMS collection and blinded assessment at 3 months         |                                                                                                       |                                                                                                                                                   |                       |
| (21 patients may reach 3 months follow up within the pilot) | 2 (10%)                                                                                               | 7 (33%)                                                                                                                                           | 11 (52%)              |
| Action                                                      | Use other pilot data and patient focus group to inform discussion with TSC to consider stopping trial | Use other pilot data and patient focus group to inform discussion with TSC regarding strategies for improvement and consider changes to processes | Proceed to main trial |

### Focus Groups

Participant focus groups will explore the study pathway and attitudes towards randomisation and blinding. The challenges of the study will be discussed, and the results will be used to further refine recruitment procedures, study information presentation and delivery, and training for clinical and research teams at sites.

Participants who agree to be contacted will be invited to take part in focus groups as part of the pilot phase. The focus groups will be held at the Botnar Research Centre in Oxford in the first instance. If participants from other sites express significant interest, efforts will be made to organise groups locally. All focus groups will be audio recorded and transcribed by a professional transcribing firm routinely sourced by the University of Oxford and versed in dealing with patient data. A confidentiality agreement will be put in place and any identifying information appearing in focus group transcripts will be removed as soon as possible following transcription to minimise risk of participant identification. Audio files will be treated as identifying data and will be excluded from archiving and sharing.

## 7.2. Study Participants

Patients 18 and over presenting with a single unilateral digital nerve injury appropriate for surgical repair will be considered for the NEON study.

## 7.3. Inclusion Criteria

Patients aged 18 years and above with a suspected complete digital nerve laceration in any single digit, including thumb and little finger, appropriate for surgical repair.

## 7.4. Exclusion Criteria

The participant may not enter the study if any of the following apply:

- Bilateral injury (ie both radial and ulnar digital nerves injured)
- Laceration outside the region between distal palmar crease and distal interphalangeal joint
- Closed injury
- Infected wounds
- Injuries in which a significant nerve gap exists which would preclude direct tension free surgical end-end repair
- Non-isolated or multi-level injury (ie common digital/wrist nerve injury, fracture)
- Unable to give consent
- Inability to comply with study follow-up procedures
- Date of surgery later than 10 days after injury
- Digital nerve incomplete or not present

Concomitant flexor tendon injuries and lacerations in 'critical zones' (Figure 2) will not be excluded. These will be minimisation factors in the randomisation, to balance the number of each in the two groups. Patients who are involved in current research can take part in NEON based on the clinical decision of the site team. The central study team can offer support with this decision.

[figure not shown]

**Figure 2.** Schematic diagram showing digital nerve anatomy. Grey shading denotes zone of injury for inclusion into the trial. Dark shading denotes zone of injury in the 'critical zones', a minimisation factor in the study.

## 8. PROTOCOL PROCEDURES

### 8.1. Recruitment

The study will be undertaken across NHS hospitals in the UK. Potential participants will be recruited at specialist hand clinics following presentation at A&E or minor injury units. The clinical team will identify any potential participants and, if trained, discuss the study before referring on to the research team for further information. Potential participants will be able to discuss the study further with the local research team and, if agreeable, the patient will give informed consent. The research team at each site will comprise of clinical researchers and research nurses who will be trained in Good Clinical Practice (GCP) and Consent and be listed on the delegation log.

Patients will be given an information sheet and have the study explained to them by the researcher. They will be informed that participation in the study is optional and will not affect their medical or legal rights. All patients will be made aware of the study's aims, anticipated benefits and potential risks. An adequate amount of time will be given to allow them to make a decision.

Participants in the study will not be prioritised for surgery above those who are not taking part. They will proceed through the standard clinical pathway as per routine care. Participation in the study will only influence the type of procedure received.

## **8.2. Screening and Eligibility Assessment**

Screening and eligibility assessment will take place pre-operatively, at outpatient clinics and on the day of surgery. The assessment will require examination of the finger with the dressings removed. Screening forms will be completed for each potential participant at each site, with reasons for ineligibility and non-participation documented.

The eligibility assessment is finalised in theatre via surgical exploration of the wound to confirm digital nerve injury immediately prior to randomisation.

### **Screening Study Within A Trial (SWAT)**

The screening and identification of patients potentially requiring nerve repair can be problematic. Initial diagnosis of a digital nerve injury, which directs referral for further assessment and treatment in a specialist hand unit, is usually made by non-specialist personnel in an A&E department or minor injuries unit. This can generate over-referral to secondary care as referral to a hand unit is considered a safe option, despite the lack of need for surgery. Patient characteristics which generate excess referral often include symptoms of temporary numbness caused by neuropraxia or swelling, or presentation with a very distal injury which does not warrant repair.

This SWAT will explore the ability of referring personnel to accurately diagnose and detail digital nerve injuries in the A&E department by comparing pre-referral clinician findings to specialist clinician findings. Information on injury type and suspected structure damage will be collected from A&E during screening.

The intention of this SWAT is to provide information on the appropriateness of managing nerve injuries in A&E and to improve the current routine pathway. The results could lead to more accurate referrals to hand clinic for patients with digital nerve injuries, and facilitate training for the management of injuries that do not need referral.

## **8.3. Informed Consent**

Informed consent will take place before surgery. The patient must personally sign and date the latest approved version of the Informed Consent Form before they can participate, and any study specific procedures are performed. Patients who consent but are found to have an injury that does not meet inclusion criteria during the operation will not proceed to be randomised. The informed consent process highlights this to patients.

Written and verbal versions of the Participant Information and Informed Consent will be presented to the participants detailing no less than: the exact nature of the study; what it will involve for the participant; the implications and constraints of the protocol; the known side effects and any risks involved in taking part. It will be clearly stated that the participant is free to withdraw from the study at any time for any reason without prejudice to future care, without affecting their legal rights, and with no obligation to give the reason for withdrawal.

The participant will be allowed as much time as wished to consider the information, and the opportunity to question the Investigator, their GP or other independent parties to decide whether they will participate in the study.

### **Written Informed Consent**

Written Informed Consent will be obtained by means of a dated signature of the participant and of the person who presented and obtained the Informed Consent. The person who obtained the consent must

be suitably qualified and experienced and have been authorised to do so by the Chief/Principal Investigator. A copy of the signed Informed Consent will be given to the participant, and another copy will be kept in the medical notes. The original signed form will be retained in the study site file.

### **Patient Online Consent**

Patients will be given the option to give their consent for the study online. If patients choose and after discussion with a research team member in clinic, a consent form will be emailed to patients for them to complete at home. Patients will have a copy of the Patient Information Sheet, and contact details for the local study teams and for the central team in Oxford are provided to allow the patient to ask any questions that they may have.

Patients click the link in their email to complete the form online. This process allows participants to consider the study in their own time and consent before they come to hospital for their surgery. Patients who do not complete this process before their day of operation but would still like to take part in the study can complete online in hospital if facilities are available, or can complete on paper.

## **8.4. Randomisation**

Participants will be randomised in theatre after wound exploration and confirmation of digital nerve injury diagnosis. The randomisation will follow a 1:1 allocation ratio and use a minimisation algorithm; initially simple randomisation seeding will be used and minimisation will also incorporate a “random twist” element to protect allocation concealment throughout. During wound exploration, the surgeon will identify whether the injury involves flexor tendon damage or affects a “critical zone” (Figure 2). Randomisation will be minimised according to these two factors, as well as by study site.

Randomisation will be performed using a web based automated computer generated system. The allocation system will be generated by the trial statistician and will be programmed into the Oxford Clinical Trials Research Unit (OCTRU) computer randomisation system, Registration/Randomisation and Management of Product (RRAMP). The research team at each site will conduct the randomisation via secure log-ins to the web-based system, once informed consent has been given. An emergency randomisation list prepared by the trial statistician and held securely by the trial manager will be used if RRAMP is not available.

A member of the clinical research team delegated to treatment allocation (randomising) will enter the relevant data into the online randomisation system when the participant is in theatre, and inform the operating surgeon of the allocation details. If the participant is not under general anaesthetic, this will need to be done carefully without revealing the intended treatment to protect the blinding.

## **8.5. Blinding and code-breaking**

Participants and follow-up assessors will be blinded to the randomised allocation. It is not possible to blind theatre staff.

Theatre equipment may provide visual and sound cues for participants under light or no sedation. The central study team will work with individual participating sites to agree a method of blinding that is practicable for them and meets the needs of the study.

Follow-up assessors will be blinded throughout the study to ensure objective sensory measurements. Participants in both arms will receive identical follow-up regimens to facilitate this. Site teams need to

ensure that those performing the blinded assessments are not in theatre and are not privy to unblinded discussions related to participants.

### **Unblinding**

Those in the clinical team and the central study team will not be blinded to the allocation, so no code break procedure for clinical care or safety reporting is needed. The central study team will discuss specifically with each site which techniques they will employ to ensure participant and staff blinding. In any case in which unblinding is needed, or in which it occurs accidentally, the study team will follow processes as per the OCTRU Standard Operating Procedures (SOPs).

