### **8.9.1 Clinical appointments**

Current best evidence indicates that neurosensory recovery after this injury should be assessed using a variety of sensory tests, including touch threshold and spatial discrimination (21). These are recommended standardised tests for assessment of sensory function after nerve repair from the Swedish national quality registry for hand surgery ([www.hakir.se](http://www.hakir.se)) and the American Society of Hand Therapists Clinical Assessment Recommendations (22).

NEON clinical appointments are supplementary to standard care. They will be conducted by blinded research nurses or research therapists not involved in routine patient care. Blinded assessors will receive training on the standardised administration of measures through the provision of a manual and videos.

Further training workshops will be provided by the study team if deemed necessary following pilot review. The assessments should take approximately 30 minutes per participant and be conducted in a quiet environment, preferably an office or side room.

- Touch thresholds using Weinstein Enhanced Sensory Test (WEST) monofilaments.  
Assessors will follow a standardised protocol of randomised sequences to touch, or pretend to touch, the area impacted by the digital nerve injury 5 times with monofilaments. Doing this with different weighted filaments will allow the assessor to determine the lightest filament at which 4 out of 5 applications are correctly detected.
- Static two-point discrimination test (2PD) assessed with Dellon-Mackinnon DiskCriminator.  
The 2PD threshold will be determined by trials of 10 random applications of 1 or 2 points at different widths (between 2-30mm). The smallest distance at which participants identify 1 or 2 points correctly 7 out of 10 times will be recorded as the final threshold.
- Tactile gnosis using Shape/Texture Identification (STI) test  
Assessors will follow a standardised protocol, through which participants rely on tactile gnosis to identify three shapes (circle, square and hexagon) and three textures (sets of raised dots) fixed on three different discs. Participants work through 3 levels of smaller shapes and dots.
- Complications assessment  
Complications being reviewed include: neuroma, lack of sensitivity, hypersensitivity, cold intolerance, complex regional pain syndrome and flexor tendon re-rupture, stiffness and swelling.

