### 8.9.2 Participant questionnaires

The following questionnaires will be sent to participants in the intervals above. These will be posted or emailed by the Clinical Trials Unit and can be completed by post or online. If participants do not respond within 2 weeks of sending the questionnaire, a reminder will be sent. Following this, if still no response, the central trial team may telephone the participant to collect the required data.

- Impact of Hand Nerve Disorder (I-HaND) v2  
I-HaND v2 is a validated patient-reported questionnaire specific to hand nerve disorder that measures symptoms, activity limitations and participation restrictions (23).
- Hand Health Profile of the Patient Evaluation Measure  
This questionnaire includes three sections: treatment, hand health profile and overall assessment. For the NEON study only section two, the hand health profile is being used. Similarly to I-HaND v2, this questionnaire asks about symptoms and activity limitations (24).
- EQ-5D-5L  
This questionnaire will be completed in order to calculate the EQ-5D-5L index (UK population weights) and EQ-VAS, and from this estimate quality adjusted life years for trial-based economic evaluation (25, 26).
- Complications  
Participants will report early complications 6 weeks post randomisation. These will include wound infection, delayed healing and re-opening, scar sensitivity and persistent ongoing pain.

- **Health Resource Use**

Postoperative costs and lost productivity costs attributable to the injured digital nerve will be collected during the 12-month follow-up period. This includes information on outpatient visits, community care provision, and days off work due to injury.

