### 10.2. Description of the Statistical Methods

The primary outcome measure (I-HaND v2) will be compared using a linear regression model with adjustment for the minimisation variables (critical or non-critical zone, associated tendon injury and study site). Study site will be accounted for using cluster robust variance. A secondary unadjusted analysis will also be carried out by an independent t-test. Secondary outcomes will be analysed using generalised linear models with adjustment for minimisation factors and baseline variables as appropriate. Where appropriate, repeated data will be used. Exploratory subgroup analyses will explore the possible treatment effect modification of clinically important factors (nerve injury type and critical location involvement or not), through the use of treatment by factor interaction, and will be interpreted cautiously.

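### Telephone follow-up of non-responders is assigned to a central team declared unblinded, so some I-HaND v2 scores may be collected by a caller who knows the allocation

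*Protocol*

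**What the plan says.** On who is blinded, section 8.5 states "Participants and follow-up assessors will be blinded to the randomised allocation". It links the assessor part to sensory testing: "Follow-up assessors will be blinded throughout the study to ensure objective sensory measurements". Section 8.9.1 identifies these assessors when it describes the clinical appointments: "They will be conducted by blinded research nurses or research therapists not involved in routine patient care".

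Under the Unblinding subheading of 8.5, the protocol then says "Those in the clinical team and the central study team will not be blinded to the allocation". No central role is excepted.

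On questionnaires, section 8.9.2 says "These will be posted or emailed by the Clinical Trials Unit and can be completed by post or online". A reminder follows after two weeks without a response. If that fails, "the central trial team may telephone the participant to collect the required data". The list governed by this rule opens with the I-HaND: "I-HaND v2 is a validated patient-reported questionnaire specific to hand nerve disorder". Section 10.2 confirms its standing: "The primary outcome measure (I-HaND v2) will be compared using a linear regression model". Appendix A also places the perception-of-treatment item at 12 months, and the blinding SWAT in 8.5 says participants answer it in their follow-up questionnaires.

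**The concern.** Taken together, these statements give the last step of primary-outcome collection to a group the protocol describes as aware of the allocation. I-HaND v2 covers symptoms, activity limits and participation, and answers to such items can be affected by how a caller words, explains or prompts them. If that influence differed by arm, it would enter the primary contrast directly. A careless remark could also reveal the allocation to the participant.

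The perceived-treatment question is exposed in the same way. Put by telephone, it would be asked by someone who may know the answer, so the check on blinding could be affected along with the outcome. The SWAT questions participants and clinic assessors but not callers, so it would not show a problem on the caller's side.

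**Working it through.** **Does the protocol shield the caller?**

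1. Section 8.5 refers to the central study team and 8.9.2 to the central trial team. No second team is defined, so I read them as the same group.
2. Knowledge of allocation is realistic. Section 8.8 has the surgeon record whether the allocated procedure was followed, 11.3 has the central team validate and query site-entered data, and 8.4 has the trial manager hold the emergency randomisation list.
3. The blinded assessors in 8.5 and 8.9.1 are clinic staff doing sensory tests. The duty in 8.5 to keep assessors out of theatre and away from unblinded discussion falls on site teams.
4. The SOPs cited under Unblinding concern what to do when unblinding is needed or has happened. They are not cited as limiting what a caller may see.

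No passage blinds the caller, restricts the caller's access, requires a script or records how a questionnaire was completed.

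**The plan's own figure.** The inputs from 10.3 are a difference of 7, SD 21, two-sided 5% and 90% power.

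- Normal approximation: n = 2 × (1.960 + 1.282)² × (21/7)² = 189.1, or 190 per arm.
- Noncentral t: power is 89.99% at 190 and 90.13% at 191, so the stated 191 is right.
- 382 / 0.80 = 477.5, which rounds up to the stated 478.

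The sample size reproduces and is not affected by this point.

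**Scale, for illustration only.** Let f be the share of I-HaND scores taken by telephone, assumed equal in both arms, and b the between-arm shift caused by the caller among those scores. The protocol gives neither, so both are assumptions.

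- Bias in the mean difference = f × b.
- SE = 21 × √(2/191) = 2.15 points.
- Type I error = Φ(−1.96 + bias/SE) + Φ(−1.96 − bias/SE).
- Power at 7 points if the bias runs towards the null = Φ((7 − bias)/SE − 1.96). With no bias this is 90%.

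| f | b (points) | Bias (points) | % of 7 | Type I error | Power, bias towards null |
|---|---|---|---|---|---|
| 5% | 2 | 0.10 | 1.4% | 5.0% | 89.5% |
| 10% | 3.5 | 0.35 | 5.0% | 5.3% | 87.2% |
| 20% | 3.5 | 0.70 | 10.0% | 6.2% | 83.4% |
| 20% | 7 | 1.40 | 20.0% | 10.0% | 74.1% |
| 30% | 5 | 1.50 | 21.4% | 10.7% | 72.6% |
| 30% | 7 | 2.10 | 30.0% | 16.5% | 62.6% |

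The upper rows are negligible against an SE of 2.15. The lower rows are not, but they need both a large telephone share and an arm-dependent shift close to the full target difference.

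**The case against.** A reader might infer that the protocol contradicts its own assessor-blinding claim, with the caller acting as an unblinded outcome assessor. The text does not support this. The claim in 8.5 covers participants and follow-up assessors, ties the latter to sensory measurement, and openly states that the central team is not blinded. The caller becomes an assessor only by relabelling.

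It is also tempting to say that part of the primary outcome is rated unblinded. I-HaND is patient-reported, and on the telephone the score still comes from a participant who is meant to be blinded. Calling is a discretionary last step after post or online completion and a reminder, so such scores may arise but need not.

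The SWAT text in 8.5 does warn that knowing the allocation can matter for patient-reported outcomes. For such an outcome, the natural reading is the participant's own knowledge, not the caller's.

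Two further points have weight. A mode effect that is the same in both arms cancels when the telephone share is also the same, so only an arm-dependent shift does harm. And calls recover scores that would otherwise be missing, which matters because 10.7 bases the principal analysis on observed data and 10.3 allows for 20% missing. Telephone retrieval is worth keeping.

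It can also be said that database access, call scripts and sensitivity analyses belong in SOPs, the data management plan or the SAP. That is fair for the supportive analysis. It does not answer the main point, because the protocol itself states that the callers' team is unblinded, and working practice that separates callers would run against that wording.

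**Conclusion.** The point stands as a gap in a stated procedure. As written, 8.5 and 8.9.2 allow some I-HaND v2 scores, and the 12-month perceived-treatment answers, to be collected by a caller who knows the allocation. The exposure is prompting or accidental disclosure.

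A reader might take a bias of, say, 0.3 to 1.5 points as established. It is not: that range follows only from assuming a 10–30% telephone share and a 3–5 point shift (0.10 × 3 = 0.3; 0.30 × 5 = 1.5), and its low end moves the type I error only to about 5.2%. No size can be derived from the protocol. The effect is small unless share and shift are both large. The case for acting rests on low cost, the importance of the outcome, and the fact that mode of completion cannot be reliably reconstructed later if it is not recorded.

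**What to change.** - In 8.5, limit the statement that the central team is unblinded to the roles that need the allocation.
- In 8.9.2, state that telephone collection is done by existing central staff without access to allocation or operation forms, who read the questionnaire from a fixed script that does not discuss the operation.
- Record mode of completion for each questionnaire. This makes possible a supportive analysis without telephone-collected I-HaND scores, which can be specified in the SAP. Telephone responders are a selected group, so that analysis is a check and does not replace blinding the caller.

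The cost is a database permission, a script and one data field. The downside is organisational: calling must be separated from data-query and allocation tasks within the central team. Sample size, visits and surgical procedures do not change, and telephone retrieval is kept.
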